**Fig 3 pone.0281991.g003:**
[figure not shown]
Representation of a linear chain transmission study [30].

The initial phase of this experiment will be similar to the first experiment, from clicking on the research link right up until the surprise recall test.

Following this, the experiments differ because, after this recall activity, the participant will receive a further instruction: “*Now*, *please transmit the information you obtained from the reading material to someone else by writing it here*. *You have 10 minutes to complete this activity*.” This transmission activity was conceived with the idea of testing whether what the person remembers at first is what they transmit when requested (Fig 4). At the end of this activity, a self-reporting step will take place followed by a message of acknowledgement and appreciation before being removed from the platform. The product of the information recall will undergo a spelling and grammar check, carried out by the researcher the information will then be directed to the next participant in the chain (corresponding to the 2nd generation). This entire process is repeated until the fourth and final participant in the chain is reached.

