### Sample size

Individuals aged 18 years and older with access to the Internet will be selected to participate in the research. The recruitment of volunteers will be carried out through the dissemination of the survey on social networks such as Instagram, Twitter, Facebook, WhatsApp, and E-mail. To determine the sample size for the recall stage, we used the G*Power 3.1.9.7 software [25]. We conducted an *a priori* analysis to determine both the sample size and its power. As a basis for the study, we took the effect size (Odds ratio = 1.81) in a study by Bonin et al. [26] as it is the most recent study that brings memory-related variables and employs the same statistical test that we propose to use. We calculated a sample size of 327 people with an explanatory power of 95% and z = 1.64. The default for Pr(y = 1|x = 1)H0 in the G*Power software is 0.2 (i.e., a 20% probability of the event occurring if the null hypothesis is true). However, we use 0.1 to obtain an even more reliable sample size for the phenomenon we are investigating. We consider an α of 0.05, a Power (1-β err prob) of 0.95, R^2^; = 0, and normal distribution. Fig 1 presents the parameters used for this calculation.

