**Fig 1 pone.0281991.g001:**
[figure not shown]
Parameters used to calculate the sample size based on a power analysis.

The calculation for the transmission stage was based on the same parameters. However, as this stage will be conducted in transmission chains of four people each, we divided the total number of 327 people by 4 and rounded the result to the nearest whole number, arriving at a total of 21 chains per text used and 336 participants (an increase of 9 people from the calculated sample).

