## Data collection procedure

### Recall stage

The first experiment aims to test the hypothesis on the recall of information related to COVID-19 when it is presented by a prestigious role model. The entire experiment will be carried out online, through a platform specifically developed for research of this nature, by the Laboratory of Ecology and Evolution of Social-ecological Systems at the Federal University of Pernambuco.

The protocol, adapted from a study by Silva et al. [19], involves offering reading material to a participant, immediately followed by a distraction activity, and then conducting a surprise recall test of the information that was read (Fig 2).

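### The plan does not provide for using the recall texts of first-generation chain members to test Hypothesis 2, which forgoes about 10% to 26% more participants for that test

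*Protocol article*

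**What the plan says.** All references are to the protocol article.

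- **Recall stage.** The recall hypothesis is tied to experiment 1: "The first experiment aims to test the hypothesis on the recall of information related to COVID-19".
- **Transmission stage.** The transmission hypothesis is tied to experiment 2. The first person in a chain reads the material, is distracted, and then recalls it. On the shared procedure: "The initial phase of this experiment will be similar to the first experiment". The shared part runs from the research link to the surprise recall test. The point of divergence is then given: "the experiments differ because, after this recall activity, the participant will receive a further instruction".
- **Sample size.** For the recall stage: "We calculated a sample size of 327 people with an explanatory power of 95% and z = 1.64". For the transmission stage: "arriving at a total of 21 chains per text used and 336 participants". The Transmission stage section instead gives 16 chains per condition (64 in all), and the Abstract gives eight chains per story.
- **Data analysis.** One multilevel logistic model is given for both hypotheses, with a random participant effect and role model as the fixed effect. The section neither limits Hypothesis 2 to the recall-stage sample nor says that any recall text from the chains will be added to it.

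**The concern.** Under this procedure a first-generation chain member supplies what Hypothesis 2 needs: an original text in one of the four role-model versions, the same distraction task, and a recall text scored on the same seven propositions. The member depends on nobody earlier in the chain. The transmit instruction comes after the recall text is written, so it cannot change that text. Members of generations 2 to 4 are different, because they read another participant's reproduction.

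With one hypothesis assigned to each experiment and no provision for pooling, the natural reading is that first-generation recall does not enter the test of Hypothesis 2. What is at stake is precision in comparing the prestigious source with the other three, using data that will be collected anyway. The choice should be fixed beforehand. Made after the data are seen, it would be open to the charge of having been chosen for its result, and pooling all four generations by default would bring in people who never saw an original text.

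**Working it through.** **1. Reproduce the planned 327.** Inputs from Sample size: odds ratio 1.81, baseline probability 0.1, R² = 0, normal covariate, and "We consider an α of 0.05, a Power (1-β err prob) of 0.95". The stated z = 1.64 implies a one-sided test. For a logistic Wald test with one standard normal covariate and variance correction:

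N = (z_α √V0 + z_power √V1)² / (ln OR)²

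Here ln 1.81 = 0.5933, V0 = 10.016, V1 = 11.221, and both z values are 1.645. This gives N = 326.2, rounded up to 327. The figure reproduces.

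**2. Reproduce the chain count.** 327 / 4 people per chain / 4 texts = 20.44, rounded up to 21 chains per text. 21 × 4 × 4 = 336 people, as stated.

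**3. Count the first-generation members.** There is one per chain, so the number is chains per text × 4 texts. The standard-error ratio is √(327 / N pooled). The last column is power on the plan's own one-covariate model.

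| Chains per text | Where stated | Generation 1 | Pooled N | Increase | SE ratio | Power, plan's model |
|---|---|---|---|---|---|---|
| none added | – | 0 | 327 | – | 1 | 95.0% |
| 8 | Abstract | 32 | 359 | 9.8% | 0.954 | 96.4% |
| 16 | Transmission stage | 64 | 391 | 19.6% | 0.915 | 97.4% |
| 21 | Sample size | 84 | 411 | 25.7% | 0.892 | 97.9% |

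**4. Consider the comparison actually asked.** The power in step 3 is only indicative, because the planned analysis has a four-level factor, not one normal covariate. The research question sets prestige against each other source, with 327 / 4 = 81.75 people per text. As an illustration, take one pairwise contrast at odds ratio 1.81, two-sided 5%, seven binary items per person, and a normally distributed participant effect on the logit scale. Each person's proportion recalled is compared by normal approximation:

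power = Φ( (m1 − m0) / √((v0 + v1)/n) − 1.96 )

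At baseline 0.1 (for a participant with zero random effect) and participant SD 1.0, m0 = 0.134, m1 = 0.206, v0 = 0.0274 and v1 = 0.0425. With n = 81.75 the standard error is √(0.0699/81.75) = 0.0292, and power is about 70%. The participant SD and the 40% baseline are assumptions, since the article gives neither; the 10% baseline is its own input.

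| Baseline | Participant SD | N = 327 | 359 | 391 | 411 |
|---|---|---|---|---|---|
| 10% | 0.5 | 87.2% | 90.0% | 92.3% | 93.4% |
| 10% | 1.0 | 69.9% | 73.9% | 77.4% | 79.4% |
| 10% | 1.5 | 48.8% | 52.5% | 56.0% | 58.1% |
| 40% | 0.5 | 98.5% | 99.1% | 99.5% | 99.6% |
| 40% | 1.0 | 83.1% | 86.3% | 89.1% | 90.5% |
| 40% | 1.5 | 57.3% | 61.2% | 64.9% | 67.1% |

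Across these settings pooling adds between about 1 and 10 percentage points of power. The gain is smallest where power is already near 100%.

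**The case against.** **Separate samples are a valid choice.** Testing each hypothesis on its own experiment is ordinary practice, and nothing in the article is made wrong by it. This stands: the point concerns efficiency only.

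**The exclusion is inferred.** A reader might conclude that Hypothesis 2 is tested only on the recall-stage sample. The article does not say so, and Data analysis sets no restriction by stage. Analysis sets are also often left to a statistical analysis plan. What can be said is that the stated allocation of hypotheses points to separate use and that no provision for pooling is made. If pooling was intended, one sentence would settle it.

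**The procedures may not be identical.** A reader might infer that first-generation members complete exactly the recall experiment. The article says similar, and only up to the recall test. Two practical differences follow:
- The Data exclusion criteria remove anyone who abandons before the end, and chain members face a further writing task of up to 10 minutes. Their recall would pass a heavier completion filter. A stage term does not correct dropout that differs by role model.
- No listed criterion stops a person from joining both experiments. The second recall test would then be no surprise, and the samples would overlap.

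Both need handling in the fix. Neither removes the gain, because the text is randomised and role models can be compared within each stage.

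**The headline size.** A reader might take 26% as the figure. It needs 21 chains per text, whereas the Transmission stage section itself gives 16, which yields 19.6%.

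**Power is already 95%.** On the plan's own model pooling adds only 1 to 3 points. That is correct for that model, but the model is not the four-source comparison the trial will make.

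**Conclusion.** The concern holds as a missed gain in precision. First-generation recall texts are suitable for Hypothesis 2, and the plan makes no provision for using them there. Using them would add 32, 64 or 84 people to 327, about 10% to 26%, and cut standard errors by about 5% to 11%. No single percentage can be given until the conflicting 8, 16 and 21 chains per text are reconciled. At odds ratio 1.81 and an assumed participant SD of 1.0, power for one pairwise contrast would rise from about 70% to 74–79% at 10% baseline recall, and from about 83% to 86–91% at 40%.

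The documents do not support any claim of bias or of an invalid test. The gain assumes that the planned numbers complete and are not double-counted, and that the role-model effect is comparable in the two stages.

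**What to change.** In Data analysis, before data are examined, state that:

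1. Hypothesis 2 is tested on all recall-stage participants plus the recall texts of chain generation 1; generations 2 to 4 are not included.
2. Stage (recall or transmission) enters the model as a fixed effect.
3. Each person counts once, by first participation.
4. A generation-1 recall text is kept even if the later transmit task is abandoned, unless the volunteer withdraws the data. The Data exclusion criteria need a matching exception; their other rules are unchanged.
5. The recall-stage-only fit is reported as a sensitivity analysis.

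Separately, reconcile the number of chains per text across the Abstract, Sample size and Transmission stage.

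The cost is a few sentences and a check for repeat participation, with no added participant or procedure. There is a small price: the tests of Hypotheses 1 and 2 would share the generation-1 participants and no longer rest on fully separate samples, and pooling relies on a comparable role-model effect across stages. The sensitivity fit lets a reader see whether the conclusion depends on pooling.

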**Fig 4 pone.0281991.g004:**
[figure not shown]
Representation of the information transmission experiment through a linear transmission chain. Figure based on the protocol adapted from Jiménez et al. [31].

### Data exclusion criteria

Data referring to the following will be excluded from the survey:

Volunteers who participate but are under 18 years of age.Volunteers who abandon the research before the end of the experiment.Volunteers who request the exclusion of their data from the survey.Volunteers who did not complete the attention test/distraction activity.

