**Fig 2 pone.0281991.g002:**
[figure not shown]
Recall experiment to be performed in Experiment I. Figure based on the protocol adapted from Silva et al. [18].

Upon clicking the research link, the participant will see a brief presentation of the research, followed by the consent and authorization forms to publish the data (referring to the TCLE). After accepting to participate, the volunteer will go to the next page, which will contain a form (S2 File) to fill out their data (gender, age, education, occupation, state where they live), region (urban or rural), education level, income, political inclination, and religion. The participants will then be directed to the next page, where there will be an alert, “*Now you will be asked to read a short text*. *Please read carefully as some questions will be asked later*.” after which the participant will be directed to one of the texts previously described. The texts will be randomized by the platform’s algorithm before being made available to each participant. After reading the text, they will be directed to a short attention test, which will verify whether the participant is paying attention to the experiment and also serve as a distraction activity. The test will consist of identifying certain figures (S3 File). Each page will have a two-minute time limit, which is an important step, as it ensures a standardized time for all the participants.

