Finally, the volunteer will undergo a recall test, where they will be instructed to recount their respective reading text as accurately as possible. The instructions are as follows: “*Write down what you can remember about the text you read previously*. *Be as accurate as possible and don’t worry if you cannot remember all of the information*. *You have 10 minutes to complete this activity*.” At the end of the activity, a self-reporting stage of multiple-choice questions (S4 File) will follow with: [i] Who do you trust to seek information about COVID-19? (Participants can choose more than one option, and the alternatives will be health professionals, family members, friends, politicians, among other day-to-day personalities) [ii] What is your biggest source of information about COVID-19? (They can choose more than one option, and the alternatives range from online to physical media, such as newspapers and magazines) [iii] Have you been affected by COVID-19? (The options here will be yes or no, if yes, they will be asked to what extent they were affected) [iv] Has any member of your family been affected by COVID-19? (The options are the same as for the previous question) [v] Have you been vaccinated against COVID-19? The objective of this step is to perform data triangulation between the model that the person claims to follow and the factor that influenced the recall. Upon completion, the participant will see a message of acknowledgment and appreciation and will then be removed from the platform.

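### The abandonment exclusion most naturally covers people who leave at the closing questionnaire, after the outcome text is written; the end point should be defined as submission of that text (minor)

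*Protocol article*

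**What the plan says.** All places are in the protocol article.

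- **Randomisation** (Recall stage): "The texts will be randomized by the platform’s algorithm before being made available to each participant". Anyone who leaves after reading therefore leaves after randomisation.
- **Order, recall stage:** the participant reads the text, does the attention test and writes the recall. Then: "At the end of the activity, a self-reporting stage of multiple-choice questions (S4 File) will follow". The closing message comes last: "Upon completion, the participant will see a message of acknowledgment and appreciation".
- **Order, transmission stage:** the recall text is followed by the transmission text. Then: "At the end of this activity, a self-reporting step will take place followed by a message of acknowledgement and appreciation". The Abstract also places the questionnaire at the end of the experiment.
- **Exclusions** (Data exclusion criteria): the list opens with "Data referring to the following will be excluded from the survey". It includes "Volunteers who abandon the research before the end of the experiment" and, as a separate entry, "Volunteers who request the exclusion of their data from the survey". No exception is made for people who have already produced the outcome.
- **Analysis** (Data analysis): each proposition is scored as remembered or not. The model has type of role model as fixed effect and participant as random effect. The questionnaire is given a triangulation purpose only (Recall stage).

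**The concern.** A participant who closes the browser during the questionnaire has been randomised, has read the assigned text and has written everything the main model needs. Only the triangulation answers are missing. On the natural reading of the exclusion rule, the whole record is dropped all the same.

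Two things are at stake. First, the comparison of sources is then made among people selected by what they did after exposure to the source. If leaving differs between text versions and leavers also recall differently, the estimated odds ratio between sources shifts with no true effect. Second, usable outcomes are lost even where there is no bias, and the sample size contains no allowance for exclusions.

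The rule is not needed to respect withdrawal, since removal on request is listed separately.

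**Working it through.** **1. Who is affected, by point of leaving**

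| Leaves | Outcome text written? | Excluded on the natural reading? | Recoverable by changing the rule? |
|---|---|---|---|
| Before writing the recall | No | Yes | No |
| Transmission stage, between the two texts | Recall text only | Yes | Recall text at most |
| At the questionnaire | Yes, all of it | Yes | Yes, if the platform has saved it |

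Only people in the last row lose a complete outcome.

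**2. The plan's own sample size**

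Inputs from Sample size: odds ratio 1.81, event probability 0.1, α = 0.05 with z = 1.64 (so one-sided), power 0.95, R² = 0, normal covariate. The formula is a Wald test in logistic regression on one standard normal covariate, with variance correction:

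N = (z_α √V0 + z_β √V1)² / b²

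- b = ln 1.81 = 0.593.
- V1 is the unit variance of the slope under the alternative (intercept ln(0.1/0.9)): 11.221, root 3.350.
- V0 is the unit variance under the null at the same overall event rate, 0.1125: 1/(0.1125 × 0.8875) = 10.016, root 3.165.
- z_α = z_β = 1.645.

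N = (1.645 × 3.165 + 1.645 × 3.350)² / 0.593² = 326.2, rounded up to **327**. The stated figure reproduces and holds no margin for exclusions. The 9 extra people in the transmission stage (336 − 327) come from rounding to whole chains.

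**3. Precision lost**

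The loss rates are assumptions, because the article gives none. The calculation also assumes that 327 are enrolled and that those excluded are not replaced.

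Power = Φ[(b√n − z_α √V0) / √V1]

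| Assumed loss | n = 327 × (1 − loss) | Power |
|---|---|---|
| 0% | 327 | 95.0% |
| 5% | 310.7 | 94.2% |
| 10% | 294.3 | 93.1% |
| 20% | 261.6 | 90.5% |

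**4. Bias, by illustration**

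Assume true recall of 50% under both of two text versions, and that a fraction a leaves at the questionnaire with recall of 30%. Recall among those kept is (0.5 − 0.3a)/(1 − a).

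- a = 5% against 15%: 0.485/0.95 = 51.1% and 0.455/0.85 = 53.5%. Odds 1.043 and 1.152, spurious odds ratio **1.10**.
- a = 2% against 6%: 50.4% and 51.3%, odds ratio **1.04**.
- a = 10% in both: 52.2% in both, odds ratio **1.00**. Leaving depends on recall but not on the text.
- Leavers recalling 50% like everyone else: 50% in both whatever a is, odds ratio **1.00**. Leaving depends on the text but not on recall.

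Both dependences are needed for bias.

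**The case against.** The strongest reply is that the end of the experiment is undefined. It could mean the end of the experimental tasks, with the questionnaire as an appendix, and then the rule already does what is proposed. That reading is possible. The Abstract and the placing of the completion message favour the other one, and either way the wording needs to settle it.

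A reader might infer that outcomes already submitted and stored are certain to be thrown away. The article does not support that: it never says that the platform stores a text before the last page.

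A reader might also infer that dislike of the assigned source will drive people out and bias the result. Several points weaken this:

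- Selection of the information used says that the sources are unnamed and chosen to agree with each participant's positions and tastes.
- Ethical aspects offers a reward for full completion.
- The group at issue has already done all the writing and stops only at a multiple-choice step. Aversion to the source would more plausibly act earlier, before any outcome exists.

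Whether the matching works is unknown, so differential leaving is not ruled out, but it is not shown either.

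Three further points stand. Recruitment is open and the article does not say that it stops at 327 enrolled, so excluded people might be replaced and the power loss avoided. Replacement would not remove a bias. The effect on chains is also open, since the article does not say that an exclusion removes a generation or breaks a chain. Finally, keeping the data of people who left may depend on consent terms that are not shown.

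**Conclusion.** The concern holds as a minor one. On the most natural reading, the rule excludes randomised participants who have given everything the main model needs, for a reason that arises after randomisation and that neither the analysis nor the withdrawal criterion requires.

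Its size cannot be stated. The 5% to 20% losses, and hence the fall in power to between about 94% and 90.5%, are assumed and presuppose no replacement. The odds ratios of 1.04 and 1.10 rest on a threefold difference in leaving and a 20-point recall deficit among leavers, neither of which comes from the article. Against the planning odds ratio of 1.81 they are small. The documents do not support a claim that the comparison will be biased, only that the rule allows it where leaving depends on both text and recall.

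**What to change.** - Replace the abandonment criterion with: leaving before the recall text is submitted (recall stage), or before the recall and transmission texts are submitted (transmission stage).
- Have the platform save each text at submission.
- Keep submitted outcomes unless the participant asks for removal, and as the consent terms allow.
- Treat unanswered self-report items as missing in the triangulation only.
- Report everyone who leaves after seeing a text, by text version and point of leaving. People who leave before writing cannot be recovered, and this count is the only view of whether their leaving differs between versions.

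The cost is one sentence in the exclusion criteria, a check that the platform saves at submission, and a check of the consent wording. The downside is that some included participants will lack self-report answers.
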